**Planned statistical methods**

Test of the intervention: The effect of the intervention will be examined using the treatment group by time-point interaction term from a multi-level, mixed effects, regression model analysis combining both time-points (baseline and 4 months). The primary endpoint is HADS total score at 4 months, for which the interaction component relating to 4 months (relative to baseline) will be used.

The primary analysis will take the form of an intention-to-treat analysis using complete cases. This will be supplemented by a sensitivity analysis using multiple imputation, allowing us to assess the robustness of the results against missing values (see below). Other sensitivity analyses will be conducted as appropriate (see below). Analysis will be conducted using Stata 15 and an alpha level of 5%.

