**Planned statistical methods**

Analysis of secondary outcomes:

All of the secondary outcomes will be treated as longitudinal continuous variables. For each secondary outcome, the effect of the intervention will be examined using the 4-month trial arm by time-point interaction term from the mixed effects model. The model will have two levels: time-points within patients. Random effects will be applied to the patient-specific intercepts.

- Fixed effects: trial arm, time-point, arm x time-point, design variables (hospital site, sex), other pre-specified covariates and additional covariates (see Choice of Covariates, below).
- Random effects: patient.

Sensitivity analysis

See relevant section below

Alternative tests if violation of distributional assumptions

See distributional tests below.

1. **Sensitivity analysis**

All of the above primary and secondary analyses will be supplemented with at least one sensitivity analysis where appropriate.

Imputation methods will be used to impute missing values at both time points and the main analysis re-run using this data. Imputation will be done in two stages: first, missing baseline values will be imputed using all available variables at baseline, but excluding treatment arm; second, missing values at 4 months follow-up will be imputed, using the full set of variables and including the interaction term between treatment arm and time-point (for consistency with the analysis model). If missing data at baseline is under 5% these will be imputed with simple regression imputation, otherwise multiple imputation. Follow-up values will utilise multiple imputation.

The extent of the missing data will determine how many MI datasets will be generated.

Additional sensitivity analyses will be conducted where the outcome variable does not match the distributional assumptions of the model, and/or if trial-arm imbalance on multiple covariates is present.

1. **Distributional tests**

The distribution of each outcome variable will be examined. If for any of these, their measure of skewness or kurtosis exceeds 1 we will consider them non-normal and p-values will be validated using a bootstrap method (see Bootstrapping, below).

1. **Bootstrapping**

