Bootstrapping of standard errors will be applied for any non-normal outcome variable and p-values and 95% confidence intervals derived using these. To enable bootstrapping we will use Stata to generate a set of pseudorandom numbers to act as seeds for each bootstrap analysis; providing there are enough non-normal outcomes to justify this.

1. **Choice of covariates**

The covariates to be included in all primary and secondary analyses will be selected as described below.

A pre-specified group of covariates will be included as listed in Table 1. This list includes the study “design factors”, used as part of the stratification procedure for randomising allocation to trial arms (hospital site and gender), plus two variables considered prognostic of the outcomes: age and current anxiety/depression medication.

Table 2 lists additional available covariates. We will look for imbalance between trial arms on each of these and include those with a standardised mean difference between arms of >0.25 in the primary analysis model. Some categories within variables may be collapsed; the choices here will be determined by descriptive analysis of baseline values prior to any endpoint analysis.

| **Table 1** | |
| --- | --- |
| **Pre-specified covariates** | **Description** |
| Gender (design factor) | Two levels |
| Hospital site (design factor) | Categorical |
| Age | Continuous |
| Medication for depression or anxiety | Never taken/Currently taking/Taken in the past |

| **Table 2** | | |
| --- | --- | --- |
| **Additional available covariates** | **Description** | |
| Highest qualification | Categorical |  |
| BMI | Continuous | |
| Ethnicity | Categorical | |
| Marital status | Two levels: Married/in relationship versus single | |
| Time from baseline to measurement (in days) | Continuous | |
| Employment status | Categorical | |
| Smoking status | Never/Passive/Ex/Smoker | |
| Alcohol units per month | Continuous | |
| Age at first cardiovascular event | 0-18, 19-24, 25-33, 34-44, 45-54, 55-64, 65 or older | |
| Number of co-morbidities | Continuous | |
| Number of different previous cardiovascular event | Continuous | |
| Psychological therapies for anxiety or depression | Never received/Currently receiving/Received in the past | |

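### The primary model takes in extra covariates because of chance imbalance between arms, which gains nothing in complete pairs and can cost patients

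*SAP*

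**What the plan says.** The section Choice of covariates sets up two tiers.

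- **Fixed tier.** "A pre-specified group of covariates will be included as listed in Table 1". These are gender and hospital site as design factors, "plus two variables considered prognostic of the outcomes: age and current anxiety/depression medication".
- **Conditional tier.** For the 12 variables of Table 2 the instruction is: "We will look for imbalance between trial arms on each of these and include those with a standardised mean difference between arms of >0.25". The sentence goes on to name the primary model as the one they enter. No prognostic criterion is attached to them. Categories may be merged first, but "the choices here will be determined by descriptive analysis of baseline values prior to any endpoint analysis".

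Three other parts of the SAP bear on this.

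- Under Planned statistical methods for the primary outcome, "The primary analysis will take the form of an intention-to-treat analysis using complete cases". The treatment effect is the arm-by-time-point interaction, with HADS at baseline and at 4 months both as outcomes. Under Analysis method, covariates are listed as fixed effects, and the only interaction named is arm by time-point.
- Under Sensitivity analysis, imputation of missing values, including baseline values, belongs to a supplementary re-run. No rule covers a missing covariate in the primary model.
- The same section promises further sensitivity analyses "if trial-arm imbalance on multiple covariates is present".

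**The concern.** In a randomised trial a between-arm difference in a baseline variable arises by chance, and its size does not show whether the variable predicts HADS. The screen can therefore admit an unrelated variable and leave out a balanced but strong predictor. The covariate list of the primary model is not known until the arms have been compared at baseline.

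The practical stake is the analysed sample. In a complete-case model, a selected covariate with gaps removes every patient in whom it is missing. It would be hard to defend losing patients from the primary analysis for a variable that chance put there.

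A second problem lies in the list itself. The number of days to the follow-up measurement is fixed only after randomisation and could differ by arm for reasons connected with treatment. Patients without follow-up have no such value. It is not a baseline characteristic, so a rule about baseline imbalance cannot sensibly apply to it.

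**Working it through.** **Inputs.** All are from the SAP section Sample size unless stated: effect 0.4 SD, 90% power, baseline to follow-up correlation 0.5, 20% drop-out; 119 and 121 at baseline; 84 and 105 with the primary outcome. Alpha is 5% (Planned statistical methods), taken as two-sided. The threshold of 0.25 and the 12 variables are from Choice of covariates.

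**1. The plan's own figures.** With residual SD √(1 − 0.5²) = 0.866:
- n per arm = 2 × [0.866 × (1.960 + 1.282)/0.4]² = 98.5 (plan: 98), and 98/0.8 = 122.5, rounded up to 123 (plan: 123).
- Power at 84 and 105: SE = 0.866 × √(1/84 + 1/105) = 0.1268; 0.4/0.1268 − 1.960 = 1.195; power 88.4% (plan: 88%).

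**2. How often chance triggers the rule.** Under randomisation the standardised difference is approximately normal with mean 0 and SE √(1/n₁ + 1/n₂). Then p = 2[1 − Φ(0.25/SE)], and the chance of at least one entry among 12 is 1 − (1 − p)¹².

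| Sample used to judge imbalance | SE | p per variable | Expected entries, 12p | At least one of 12 |
|---|---|---|---|---|
| 119 and 121 | 0.129 | 5.3% | 0.63 | 48% |
| 84 and 105 | 0.146 | 8.8% | 1.05 | 67% |

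The SAP does not say which sample is meant. Without the post-randomisation variable, 11 remain and the last column becomes 45% and 64%. The calculation assumes independent variables with one standardised difference each. Several Table 2 variables have more than two categories, and the SAP defines no single difference for them.

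**3. What an added covariate does to the estimate.** In a patient with both HADS values, a time-constant main effect contributes equally to both and cancels from the within-patient change, which carries the arm-by-time term. In three simulated data sets with an imbalanced prognostic covariate:

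| Data set | Complete pairs, without / with covariate | Baseline-only patients kept, without / with covariate |
|---|---|---|
| 1 | −0.7182 / −0.7182 | −0.7119 / −0.6876 |
| 2 | −0.3586 / −0.3586 | −0.3831 / −0.3967 |
| 3 | −0.5184 / −0.5184 | −0.5482 / −0.5430 |

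In complete pairs the standard errors were also identical to four decimals. With baseline-only patients kept, the estimate moved by 0.005 to 0.024 and the standard error barely changed (for example 0.1258 to 0.1240).

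**4. What missing covariate values would cost.** The SAP gives no missingness rate for Table 2, so the range is assumed. Both arms are reduced by the same fraction and the formula in step 1 is reused.

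| Share of the 189 lost | Patients left (about) | Power |
|---|---|---|
| 0% | 189 | 88.4% |
| 5% | 180 | 86.8% |
| 10% | 170 | 84.9% |
| 20% | 151 | 80.6% |

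These powers use the plan's own basis, a residual SD of 0.866. The interaction in complete pairs is a difference in mean change, whose SD at correlation 0.5 is √(2 × (1 − 0.5)) = 1. On that basis the starting power is 78.0%. That is a separate matter; the table should be read as the loss relative to the plan's stated 88%.

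**The case against.** The rule has a real defence. The candidate list, the metric and the threshold are all fixed in advance, and outcome values play no part. Prognosis is not ignored, because age and medication enter on that ground whatever the imbalance. The loss of patients depends on missingness that the SAP does not report, and the imputation re-run would partly show its effect. All of this stands, and it limits the point to the supplementary tier.

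A reader might go further in three ways that the document does not support.

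- **Post hoc model selection.** The rule is mechanical and blind to outcome. Only its result is unknown in advance.
- **Inflated type I error.** None is shown. Simulating the rule under the null (12 prognostic covariates, 84 and 105 patients, 20,000 trials) gave 4.9% with a baseline-adjusted model and 4.3% with a follow-up-only model. In the planned model a time-constant covariate does not alter the test in complete pairs.
- **A contradiction between Sensitivity analysis and Choice of covariates.** One section adjusts the primary model for each variable over the threshold. The other adds analyses when several variables are imbalanced. The two can coexist.

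The cancellation in step 3 also means that leaving out a strong, balanced predictor costs little here. It equally removes the reason for the rule, since adjustment for an imbalanced time-constant variable then corrects nothing in complete pairs.

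**Conclusion.** The point holds in a limited form. The supplementary covariates of the primary model are chosen by chance imbalance, with about a 48% probability that at least one of 12 enters at 119 and 121 patients, given independence and one standardised difference per variable. For time-constant covariates in complete pairs the adjustment gains nothing, while any missing values in them remove patients. The cost is modest at 5% loss (88.4% to 86.8%) and reaches 80.6% at 20%; these loss rates are assumptions. Including the time to measurement is an error in the list whatever those rates are. If it were coded to vary over time, the cancellation argument would not cover it. No bias or error-rate inflation is claimed. The change is worth making before the analysis because it is cheap and settles the primary model.

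**What to change.** 1. **Fix the primary covariates:** hospital site, sex, age, anxiety/depression medication, and the anxiety/depression stratum. Sample size names that stratum as a randomisation factor, but Table 1 omits it. Do not add baseline HADS as a covariate, because it is already an outcome in the model.
2. **Move the 0.25 rule** to a labelled sensitivity analysis restricted to baseline variables, with the time to measurement removed. State which sample is used to judge imbalance and how the difference is computed for variables with several categories.
3. **Impute missing baseline covariates in the primary analysis** without using treatment arm, by the rule already under Sensitivity analysis: regression imputation below 5% missing, multiple imputation otherwise. Reword the complete-case statement so that no patient with HADS data is dropped for a missing covariate.

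The cost is SAP wording, plus pooling over imputed data sets if the 5% limit is passed. The planned sample size does not change, because its calculation uses only the baseline HADS correlation. The downside is that a variable imbalanced by chance is adjusted for only in the sensitivity analysis.

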**Sample size**

The WS3 pilot trial had a planned total sample size of 108, using 1:1 random assignment to Home-MCT plus usual CR or usual CR alone. Participant allocation was undertaken by a blinded statistician using a sequence based on randomised blocks of size 6 and 4, stratified by site, gender and whether they suffered from anxiety, depression or both.

WS3+ utilised an identical randomisation procedure and was powered to detect an effect size of 0.4 on total HADS score at 90% power, assuming a 0.5 correlation between HADS at baseline and FU 20% drop-out at 4 months follow-up (based on WS2). This indicated a total recruitment target (i.e. including the internal pilot participants) of 123 per arm, aiming to collect 4month FU on 98 of these in each arm.

In March 2020 the UK was put into lockdown as a result of the covid-19 pandemic. Covid interfered with participation in CR and also with the entry of CR attendance data into the database. Since it was unknown how long the lockdown would be in place, a decision was taken to review the data collected to date, to determine if it was feasible to halt any further data collection. The table below shows the target and achieved samples at baseline and 4 months as of 06/04/2020

WS3+ (Total Target: 246):

|  | MCT + CR | | | CR | | |
| --- | --- | --- | --- | --- | --- | --- |
|  | Target sample | Achieved sample | Number known to have completed CR | Target sample | Achieved sample | Number known to have completed CR |
| Baseline | 123 | 119 | - | 123 | 121 | - |
| 4 months FU | 98 | 76 (84)* | 58 | 98 | 100 (105)* | 61 |
| *including patients who returned the primary outcome (HADS) only | | | | | | |

On the basis of the samples for which the primary outcome at 4-months was available (MCT+CR=84; CR=105), the available power to detect the target effect of 0.4 was computed to be 88%. For the secondary outcomes (MCT+CR=76; CR=100) the power to detect an effect of 0.4 was 86%.

On the basis of the above, in discussion with the TSC it was decided that recruiting additional participants into WS3+ would have quite limited benefit, and that study resources would be better deployed at aiming to collect the outstanding 4 month FUs from current participants. This should also aim to reduce the imbalance between trial arms in the numbers with outstanding 4-month FUs to collect.

1. **Main analyses of Primary Outcomes**

*Research Null hypothesis:*

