**Analysis method**

The primary outcome is assumed to be a continuous longitudinal variable for which linear regression is appropriate. The model will have two levels: time-points within patients**.** Random effects will be applied to the patient-specific intercepts.

1. Outcome: HADS total score at baseline and 4 months.
2. Fixed effects: trial arm, time-point, arm x time-point, design variables (hospital site, sex), other pre-specified covariates and additional covariates (see Choice of Covariates, below).
3. Random effects: patient.

Time-point will be treated as a discrete variable.

In terms of the covariance matrix chosen for the mixed effects model, both an unstructured and a first order autoregressive covariance matrix will be explored. The one with the lowest Bayesian information criteria will be selected.

Alternative tests if violation of distributional assumptions

See distributional tests below.

Sensitivity analysis

See relevant section below

1. **Analyses of Secondary Outcomes**

Research hypotheses:

There are no significant differences in the secondary outcomes between usual cardiac rehabilitation (CR) and home-based (self-help) metacognitive therapy (MCT) plus usual cardiac rehabilitation at 4 months. For the secondary outcomes, tests of an intervention effect will be assessed using the mixed-effects model interaction between treatment arm and time-point.

| **Secondary outcome** | **Description** |
| --- | --- |
| HADS anxiety score | Score based on summing across the 7 anxiety-specific items from the HADS |
| HADS Depression score | Score based on summing across the 7 depression-specific items from the HADS |

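### Table 2 lets days from baseline to the 4-month form, a post-randomisation variable with no stated coding, enter the primary model when the arms differ on it

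*SAP*

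**What the plan says.** The section Choice of covariates sets one rule for every model: "The covariates to be included in all primary and secondary analyses will be selected as described below". Table 1 gives the covariates that always enter. Table 2 gives twelve more, and for these the instruction is to "include those with a standardised mean difference between arms of >0.25 in the primary analysis model". One of the twelve is "Time from baseline to measurement (in days", described only as continuous.

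The section Analysis method confirms that selected Table 2 variables become fixed effects, alongside "other pre-specified covariates and additional covariates (see Choice of Covariates, below". The treatment effect is the arm by time-point interaction from a mixed model with a baseline row and a 4-month row per patient. On the analysis set, the SAP says: "The primary analysis will take the form of an intention-to-treat analysis using complete cases".

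Nothing exempts the timing row or says what value it takes in the baseline row. The one reference to baseline data, "the choices here will be determined by descriptive analysis of baseline values prior to any endpoint analysis", concerns the collapsing of categories and does not restrict which variables are eligible.

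**The concern.** The other eleven rows describe patient characteristics and history, on which randomised arms should differ only by chance. An imbalance trigger is meant for that situation. Days to the 4-month form are fixed only when the form comes back, so arm, or a patient state that also drives HADS, can influence them. A large SMD on such a variable is then partly a signal that arm has affected it.

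Two things are at stake. First, conditioning the primary comparison on a possible consequence of arm can move the estimate away from the randomised contrast. Second, because the coding is not stated, an analyst would choose between a version that does nothing to the primary estimate and one that can change it, after the timing data are known.

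**Working it through.** **Inputs from the SAP (Sample size; Choice of covariates).** Baseline 119 (MCT+CR) v 121 (CR); HADS returned by 06/04/2020, 84 v 105; target effect 0.4; SMD threshold 0.25. The SAP gives no timing by arm, so every timing figure below is an assumption.

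**1. The plan's own figures.** With residual SD √(1 − 0.5²) = 0.866, effect 0.4 and two-sided 5% (sidedness assumed), power is 88.4% at 84 v 105 and 85.9% at 76 v 100. The SAP states 88% and 86%. These reproduce and are not at issue.

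**2. When the rule fires.** At 84 v 105, the standard error of a null SMD is √(1/84 + 1/105) = 0.146. By normal approximation, the chance that |SMD| exceeds 0.25 is:

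| True SMD in days | Chance of inclusion |
| --- | --- |
| 0 | 8.8% |
| 0.25 | 50% |
| 0.4 | 84.5% |
| 0.5 | 95.4% |

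The rule seldom admits the variable when arm has no effect on timing, and usually does when arm has a sizeable one.

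**3. What inclusion does, by coding.** With two complete rows per patient and arm, time-point and their interaction all fitted, each fitted arm-by-time mean is the observed mean less β × the mean of the covariate in that cell. Let Δ be the arm difference in mean days.

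- One value per patient: β × Δ is subtracted at both time-points and cancels, so the interaction is unchanged.
- 0 at baseline, actual days at 4 months: β × Δ is subtracted only at 4 months, so the interaction moves by −β × Δ.

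**4. An illustrative size.** Without a returned HADS at 06/04/2020: 119 − 84 = 35 (29.4%) v 121 − 105 = 16 (13.2%). Assume that all of these arrive 60 days late and that the on-time SD is 20 days.

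- Δ = (0.294 − 0.132) × 60 = 9.7 days.
- Pooled late share = 51/240 = 0.21; SD = √(20² + 0.21 × 0.79 × 60²) = 31.6 days.
- SMD = 9.7/31.6 = 0.31, above the threshold.
- If HADS differs by 0.1 to 0.3 SD per 30 days, the shift is 0.1 × 9.7/30 = 0.03 to 0.3 × 9.7/30 = 0.10 SD, or 8% to 24% of 0.4.

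The trigger is sensitive to these assumptions. If half the forms arrive, late shares are 17.5/101.5 = 17.2% v 8/113 = 7.1%, Δ is 6.1 days, SD is 27.9 and SMD is 0.22. If all arrive but 30 days late, Δ is 4.9 days, SD is 23.5 and SMD is 0.21. In neither case does the rule fire.

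**5. Simulation.** 3,000 runs per scenario of the two-row model, 84 v 105, true effect −0.40 SD, 0-then-days coding and the 0.25 rule applied. Arm shifts delay by 0.3 or 0.5 SD. An unmeasured cause has coefficient 0.6 on delay (in SD) and 0.3 or 0.5 on 4-month HADS.

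| Shift in delay | Coefficient on HADS | Mean estimate under the rule |
| --- | --- | --- |
| 0.3 | 0.3 | −0.44 |
| 0.3 | 0.5 | −0.47 |
| 0.5 | 0.3 | −0.48 |
| 0.5 | 0.5 | −0.54 |

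With the variable left out, or entered as one value per patient, the mean stayed at about −0.40. It also stayed there under the rule when either the shift or the shared cause was absent. The direction follows from the assumed signs; reversing one of them would reverse it.

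**The case against.** **The coding may be harmless.** Every other Table 2 row has one value per patient, computing a between-arm SMD needs one value per patient, and no covariate-by-time term is listed. On that reading the primary estimate is untouched. This stands as a limit on the harm. It does not justify the row, which would then do nothing for the estimate. Read literally, moreover, time from baseline is 0 in the baseline row, which is the coding that can matter.

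**Adjustment could be the repair.** If one arm is assessed later for administrative reasons and HADS drifts with time, the unadjusted contrast is the distorted one. With Δ = 9.7 days and HADS falling by 0.1, 0.2 or 0.3 SD per 30 days, a true −0.40 would appear unadjusted as −0.43, −0.46 or −0.50, and adjustment would recover −0.40. This also stands: the shift in step 4 could be bias added or bias removed, and the SAP cannot say which. But the planned model cannot separate administrative delay from delay caused by arm or by distress, so a data-triggered entry into the primary model is the wrong place to settle the question.

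**Stronger readings that the SAP does not support.**

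- A reader might infer that the plan makes an arm difference in timing likely. The Sample size section gives counts, not dates. The 35 and 16 may mix forms not yet due, withdrawals, losses and late returns, and the SAP itself assumes 20% drop-out, about 24 per arm. The remark on chasing forms, "This should also aim to reduce the imbalance between trial arms in the numbers with outstanding 4-month FUs to collect", concerns numbers outstanding.
- A reader might suppose that the self-help course was still running when forms fell due. The SAP gives no course duration.
- A reader might think that the missing value for non-responders damages the primary analysis. That analysis uses complete cases, so it does not on this ground.

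**Conclusion.** The defect in the text is clear: a variable determined after randomisation and open to influence by arm is eligible for the primary and secondary models through an imbalance trigger, with no stated coding. Depending on the coding, the row either leaves the complete-case primary estimate unchanged or makes it depend on that variable.

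The size and direction of any effect cannot be known from the SAP. The 0.03 to 0.10 SD range requires the 0-then-days coding, an arm difference of about 10 days and the assumed HADS slope; it is a possible shift and not a demonstrated bias. For it to be a bias, arm must affect timing, and timing must be tied to HADS in a way that adjustment distorts. The unequal missing follow-up at 06/04/2020 (35 v 16) makes an arm difference in timing possible and does not establish one. The change is worth making because it is cheap and protects the primary estimate, not because harm has been shown.

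**What to change.** Delete the timing row from Table 2 and state that only variables measured before randomisation can enter through the 0.25 rule. Report days from baseline to the 4-month form by arm. Examine timing only in a labelled sensitivity analysis with the coding written down, for example adjusting for actual days, set to 0 in the baseline row. The SAP should note that any such analysis, including a restriction to forms returned within a window, also conditions on a post-randomisation variable and so cannot replace the primary result.

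The cost is one row deleted and one sensitivity model added; the sample size is unaffected. The small downside is that the primary analysis would no longer correct for purely administrative differences in assessment time.
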